### 3.4 Supplementary Table S4: PROMOTe Dietary Intakes from Background Diet at Baseline and End time points.

|                                           | Baseline       |                |                |  | End            |                |                |         |
|-------------------------------------------|----------------|----------------|----------------|--|----------------|----------------|----------------|---------|
| Dietary variable                          | Females        | Males          | Total          |  | Females        | Males          | Total          | P-value |
| Energy, macronutrients, components | N=56           | N=16           | N=72           |  | N=56           | N=16           | N=72           |         |
| Energy kcal/d                             | 1504.4 (347.6) | 1797.5 (484.0) | 1569.5 (397.7) |  | 1410.6 (383.4) | 1672.4 (546.4) | 1476.0 (438.7) | 0.021*  |
| Protein g/d                               | 58.2 (15.6)    | 67.5 (11.9)    | 60.2 (15.2)    |  | 59.2 (18.0)    | 55.0 (20.2)    | 58.2 (18.4)    | 0.321   |
| Fat g/d                                   | 63.0 (19.3)    | 76.9 (26.2)    | 66.1 (21.6)    |  | 59.9 (20.1)    | 70.9 (26.4)    | 62.7 (22.1)    | 0.032*  |
| Cholesterol g/d                           | 236.2 (106.1)  | 255.0 (108.4)  | 240.3 (106.0)  |  | 253.4 (123.7)  | 178.7 (136.6)  | 234.7 (129.7)  | 0.676   |
| Carbohydrate g/d                          | 157.4 (56.8)   | 199.8 (59.9)   | 166.7 (59.6)   |  | 149.2 (55.1)   | 185.7 (60.5)   | 158.4 (58.1)   | 0.115   |
| Glucose g/d                               | 13.2 (8.2)     | 13.3 (8.1)     | 13.2 (8.1)     |  | 13.0 (8.8)     | 12.5 (5.4)     | 12.8 (8.1)     | 0.221   |
| Sugar g/d                                 | 71.5 (34.5)    | 82.8 (47.1)    | 74.0 (37.5)    |  | 65.5 (31.3)    | 82.3 (43.0)    | 69.7 (34.9)    | 0.106   |
| Oligosaccharide g/d                       | 0.9 (1.8)      | 1.0 (1.3)      | 0.9 (1.7)      |  | 0.4 (0.6)      | 0.4 (0.7)      | 0.4 (0.6)      | 0.329   |
| Starch g/d                                | 81.9 (34.9)    | 115.9 (19.1)   | 89.4 (34.9)    |  | 80.5 (34.2)    | 94.8 (33.3)    | 84.1 (34.2)    | 0.186   |
| Fibre AOAC, g/d                           | 16.5 (5.9)     | 15.9 (5.7)     | 16.3 (5.8)     |  | 15.5 (6.2)     | 18.9 (7.6)     | 16.3 (6.7)     | 0.951   |
| Fibre NSP, g/d                            | 11.6 (4.1)     | 11.0 (3.6)     | 11.4 (4.0)     |  | 11.3 (4.9)     | 12.2 (4.7)     | 11.5 (4.8)     | 0.697   |
| Minerals                           |                |                |                |  |                |                |                |         |
| Sodium mg/d                               | 1723.5 (763.8) | 2312.9 (752.6) | 1853.4 (794.0) |  | 1727.0 (640.7) | 1698.9 (698.2) | 1720.0 (648.0) | 0.341   |
| Potassium mg/d                            | 2384.2 (627.6) | 2670.0 (874.7) | 2447.2 (691.5) |  | 2252.0 (731.7) | 2649.0 (911.3) | 2351.2 (789.5) | 0.099   |
| Calcium mg/d                              | 684.5 (258.1)  | 900.9 (272.2)  | 732.2 (274.2)  |  | 652.8 (389.6)  | 724.2 (331.5)  | 670.7 (373.8)  | 0.370   |
| Magnesium mg/d                            | 226.0 (66.7)   | 266.2 (82.7)   | 234.8 (71.8)   |  | 213.0 (78.2)   | 281.2 (109.6)  | 230.0 (90.8)   | 0.466   |
| Iron mg/d                                 | 8.9 (2.4)      | 8.8 (1.9)      | 8.9 (2.3)      |  | 8.3 (3.7)      | 9.1 (4.5)      | 8.5 (3.9)      | 0.892   |
| Zinc mg/d                                 | 6.7 (2.2)      | 7.9 (1.9)      | 7.0 (2.2)      |  | 6.7 (2.5)      | 6.7 (2.7)      | 6.7 (2.6)      | 0.142   |
| Selenium µg/d                             | 37.8 (15.8)    | 41.9 (17.6)    | 38.7 (16.1)    |  | 37.6 (16.5)    | 39.3 (21.9)    | 38.0 (17.7)    | 0.998   |

|                              |                |                |                |  |                |                |        |
|------------------------------|----------------|----------------|----------------|--|----------------|----------------|--------|
| Vitamins              |                |                |                |  |                |                |        |
| Vitamin A µg/d               | 0.0 (0.0)      | 0.0 (0.0)      | 0.0 (0.0)      |  | 0.0 (0.0)      | 0.0 (0.0)      | -      |
| Thiamine mg/d                | 1.2 (0.4)      | 1.3 (0.4)      | 1.2 (0.4)      |  | 1.3 (1.3)      | 1.2 (0.4)      | 0.519  |
| Riboflavin mg/d              | 1.3 (0.5)      | 1.5 (0.5)      | 1.3 (0.5)      |  | 1.3 (0.7)      | 1.3 (0.6)      | 0.132  |
| Niacin mg/d                  | 14.5 (5.0)     | 15.0 (6.0)     | 14.6 (5.2)     |  | 15.1 (7.0)     | 16.5 (6.9)     | 0.609  |
| Vitamin B6 µ/d               | 1.5 (0.5)      | 1.6 (0.6)      | 1.5 (0.5)      |  | 1.4 (0.5)      | 1.6 (0.6)      | 0.188  |
| Vitamin B12 µg/d             | 3.5 (1.9)      | 4.4 (2.3)      | 3.7 (2.0)      |  | 2.9 (1.6)      | 2.6 (1.3)      | 0.026* |
| Folate µg/d                  | 222.1 (82.9)   | 212.5 (77.3)   | 220.0 (81.2)   |  | 183.8 (77.1)   | 212.8 (99.9)   | 0.079  |
| Vitamin C µg/d               | 91.4 (73.9)    | 61.9 (26.1)    | 84.9 (67.3)    |  | 69.9 (47.3)    | 72.4 (43.5)    | 0.084  |
| Vitamin D µg/d               | 3.5 (3.8)      | 2.9 (1.9)      | 3.3 (3.4)      |  | 2.7 (2.3)      | 2.1 (2.8)      | 0.200  |
| 25-Hydroxy D3 µg/d           | 0.0 (0.1)      | 0.0 (0.0)      | 0.0 (0.1)      |  | 0.4 (1.2)      | 0.0 (0.2)      | 0.092  |
| Vitamin D3 µg/d              | 0.3 (0.6)      | 0.6 (0.9)      | 0.4 (0.7)      |  | 0.3 (0.7)      | 0.3 (0.8)      | 0.228  |
| Vitamin E µg/d               | 8.0 (3.3)      | 8.9 (5.8)      | 8.2 (3.9)      |  | 6.2 (2.6)      | 8.2 (5.1)      | 0.014* |
| Vitamin K1 µg/d              | 78.3 (89.5)    | 54.7 (37.4)    | 73.1 (81.3)    |  | 50.2 (37.8)    | 49.1 (53.5)    | 0.442  |
| Food groups and other |                |                |                |  |                |                |        |
| Vegetables g/d               | 160 (120)      | 107 (63)       | 149 (112)      |  | 141 (64)       | 95 (61)        | 0.469  |
| Fruits g/d                   | 143.5 (104.2)  | 148.9 (107.7)  | 144.7 (104.0)  |  | 141.2 (141.5)  | 143.1 (92.2)   | 0.167  |
| Alcohol g/d                  | 9.7 (15.6)     | 18.6 (21.3)    | 11.6 (17.2)    |  | 7.7 (8.7)      | 13.5 (19.8)    | 0.063  |
| Water g/d                    | 1931.3 (625.8) | 2075.4 (840.2) | 1963.0 (673.4) |  | 1858.9 (622.3) | 1848.2 (782.2) | 0.124  |
| Missing Data (n)             | 10             | 3              | 13             |  | 20             | 4              | 24     |

All data presented as mean (standard deviation). Please note the nutritional intake from the intervention sachet is not included in these dietary data. NSP: non-starch polysaccharides. AOAC fibre comprises of the total amount of non-digestible polysaccharides, and includes e.g., lignin and resistant starches, measured with a set of methods developed by the Association of Analytical Chemists (AOAC). \* Denotes significance.

P values are within group comparisons of the total population between baseline and end of intervention performed using a two-sided paired t-test

### 3.5 Supplementary Table S5: PROMOTe Dietary Intakes from Background Diet at Baseline and End time points, with Over Reporters removed.

|                                           | Baseline          |                   |                   |  | End               |                   |                   |             |
|-------------------------------------------|-------------------|-------------------|-------------------|--|-------------------|-------------------|-------------------|-------------|
| Dietary variable                          | Females           | Males             | Total             |  | Females           | Males             | Total             | P-value     |
| Energy, macronutrients, components | N=54              | N=15              | N=69              |  | N=55              | N=15              | N=70              |             |
| Energy kcal/d                             | 1528.1
(330.0) | 1824.8
(488.1) | 1592.6
(386.2) |  | 1431.8
(366.9) | 1773.7
(439.4) | 1513.5
(407.8) | 0.010
0* |
| Protein g/d                               | 59.7 (14.0)       | 67.2 (12.3)       | 61.3 (13.9)       |  | 59.7 (18.1)       | 58.4 (17.2)       | 59.4 (17.7)       | 0.198
9  |
| Fat g/d                                   | 64.9 (17.3)       | 79.4 (25.7)       | 68.0 (20.1)       |  | 61.0 (19.4)       | 74.8 (23.8)       | 64.3 (21.1)       | 0.016
3* |
| Cholesterol g/d                           | 240.2
(106.3)  | 242.3
(102.7)  | 240.7
(104.7)  |  | 256.2
(124.3)  | 191.9
(134.9)  | 240.8
(128.4)  | 0.674
2  |
| Carbohydrate g/d                          | 161.1
(55.1)   | 205.3
(58.9)   | 170.5
(58.4)   |  | 151.4
(54.4)   | 197.0
(48.4)   | 162.3
(56.1)   | 0.136
3  |
| Glucose g/d                               | 13.4 (8.3)        | 13.5 (8.5)        | 13.4 (8.2)        |  | 13.2 (8.8)        | 13.2 (5.0)        | 13.2 (8.0)        | 0.221
6  |
| Sugar g/d                                 | 72.8 (34.6)       | 85.6 (48.1)       | 75.5 (37.7)       |  | 66.5 (31.1)       | 87.4 (41.1)       | 71.5 (34.5)       | 0.098
1  |
| Oligosaccharide g/d                       | 0.9 (1.8)         | 1.0 (1.3)         | 1.0 (1.7)         |  | 0.4 (0.6)         | 0.5 (0.7)         | 0.4 (0.6)         | 0.318
9  |
| Starch g/d                                | 84.2 (33.9)       | 118.8
(16.7)   | 91.6 (34.1)       |  | 81.5 (34.1)       | 101.3
(25.7)   | 86.2 (33.1)       | 0.267
6  |
| Fibre AOAC, g/d                           | 16.9 (5.6)        | 16.1 (5.9)        | 16.7 (5.6)        |  | 15.6 (6.2)        | 20.2 (6.6)        | 16.7 (6.5)        | 0.958
8  |
| Fibre NSP, g/d                            | 11.9 (3.9)        | 11.2 (3.7)        | 11.7 (3.9)        |  | 11.4 (4.9)        | 13.1 (3.8)        | 11.8 (4.7)        | 0.822
9  |
| Minerals                           |                   |                   |                   |  |                   |                   |                   |             |
| Sodium mg/d                               | 1770.8
(746.1) | 2346.3
(775.9) | 1894.1
(782.6) |  | 1738.8
(646.1) | 1828.8
(560.0) | 1760.3
(621.8) | 0.456
1  |
| Potassium mg/d                            | 2424.1
(607.9) | 2647.5
(909.7) | 2472.0
(680.4) |  | 2271.7
(732.5) | 2836.0
(672.4) | 2406.7
(751.8) | 0.090
8  |

|                       |                  |                  |                  |  |                  |                  |                  |             |
|-----------------------|------------------|------------------|------------------|--|------------------|------------------|------------------|-------------|
| Calcium mg/d          | 704.0
(246.6) | 928.3
(264.9) | 752.1
(264.9) |  | 661.3
(392.0) | 786.2
(264.9) | 691.1
(366.8) | 0.401
2  |
| Magnesium mg/d        | 229.6
(65.8)  | 267.9
(86.1)  | 237.8
(71.5)  |  | 215.5
(77.8)  | 298.8
(95.5)  | 235.4
(88.8)  | 0.488
1  |
| Iron mg/d             | 9.0 (2.2)        | 8.9 (2.0)        | 9.0 (2.2)        |  | 8.4 (3.7)        | 9.7 (4.2)        | 8.7 (3.8)        | 0.901
6  |
| Zinc mg/d             | 6.9 (2.0)        | 7.9 (1.9)        | 7.1 (2.0)        |  | 6.7 (2.5)        | 7.2 (2.3)        | 6.9 (2.4)        | 0.162
7  |
| Selenium µg/d         | 38.5 (15.7)      | 39.0 (14.9)      | 38.6 (15.4)      |  | 38.2 (16.3)      | 34.7 (15.7)      | 37.4 (16.0)      | 0.906
3  |
| Vitamins       |                  |                  |                  |  |                  |                  |                  |             |
| Vitamin A µg/d        | 0.0 (0.0)        | 0.0 (0.0)        | 0.0 (0.0)        |  | 0.0 (0.0)        | 0.0 (0.0)        | 0.0 (0.0)        | -           |
| Thiamine mg/d         | 1.2 (0.3)        | 1.3 (0.5)        | 1.2 (0.4)        |  | 1.4 (1.3)        | 1.3 (0.3)        | 1.4 (1.1)        | 0.555
8  |
| Riboflavin mg/d       | 1.3 (0.4)        | 1.5 (0.5)        | 1.4 (0.5)        |  | 1.3 (0.7)        | 1.4 (0.5)        | 1.3 (0.6)        | 0.210
8  |
| Niacin mg/d           | 14.8 (4.8)       | 13.9 (4.8)       | 14.6 (4.8)       |  | 15.2 (7.1)       | 16.2 (7.2)       | 15.4 (7.0)       | 0.885
8  |
| Vitamin B6 µ/d        | 1.5 (0.4)        | 1.6 (0.6)        | 1.5 (0.5)        |  | 1.4 (0.6)        | 1.7 (0.5)        | 1.5 (0.5)        | 0.162
4  |
| Vitamin B12 µg/d      | 3.6 (1.8)        | 4.0 (2.0)        | 3.7 (1.9)        |  | 2.9 (1.6)        | 2.6 (1.4)        | 2.8 (1.6)        | 0.051
7  |
| Folate µg/d           | 228.6
(78.8)  | 203.5
(73.3)  | 223.2
(77.7)  |  | 185.3
(77.7)  | 230.5
(82.8)  | 196.1
(80.4)  | 0.090
2  |
| Vitamin C µg/d        | 93.1 (75.1)      | 62.3 (27.2)      | 86.5 (68.7)      |  | 71.2 (47.3)      | 77.1 (42.5)      | 72.6 (45.8)      | 0.049
5* |
| Vitamin D µg/d        | 3.6 (3.8)        | 2.6 (1.6)        | 3.4 (3.5)        |  | 2.7 (2.4)        | 2.0 (2.9)        | 2.5 (2.5)        | 0.173
1  |
| 25-Hydroxy D3
µg/d | 0.0 (0.1)        | 0.0 (0.0)        | 0.0 (0.1)        |  | 0.4 (1.2)        | 0.1 (0.2)        | 0.3 (1.1)        | 0.090
4  |
| Vitamin D3 µg/d       | 0.3 (0.6)        | 0.5 (0.8)        | 0.4 (0.7)        |  | 0.3 (0.7)        | 0.1 (0.4)        | 0.3 (0.6)        | 0.098
2  |
| Vitamin E µg/d        | 8.2 (3.2)        | 9.3 (5.9)        | 8.4 (3.9)        |  | 6.3 (2.6)        | 8.7 (5.0)        | 6.9 (3.4)        | 0.015
3* |
| Vitamin K1 µg/d       | 80.7 (90.8)      | 54.2 (39.0)      | 75.0 (82.9)      |  | 51.4 (37.6)      | 53.0 (54.3)      | 51.8 (41.5)      | 0.588
2  |

| Food groups and other |                   |                   |                   |  |                   |                   |                   |
|------------------------------|-------------------|-------------------|-------------------|--|-------------------|-------------------|-------------------|
| Vegetables g/d               | 161.9
(122.2)  | 110.3
(64.9)   | 150.8
(113.9)  |  | 143.2
(63.4)   | 103.2
(55.8)   | 133.6
(63.4)   |
| Fruits g/d                   | 145.5
(105.6)  | 152.4
(111.7)  | 147.0
(105.9)  |  | 142.6
(143.3)  | 154.4
(87.5)   | 145.4
(131.3)  |
| Alcohol g/d                  | 8.2 (13.1)        | 18.0 (22.2)       | 10.3 (15.8)       |  | 7.9 (8.8)         | 14.7 (20.3)       | 9.5 (12.6)        |
| Water g/d                    | 1956.7
(626.8) | 2023.9
(855.8) | 1971.1
(674.1) |  | 1865.7
(630.1) | 1975.9
(676.8) | 1892.0
(635.6) |
| Missing Data (n)             | 11                | 3                 | 14                |  | 20                | 4                 | 24                |

All data presented as mean (standard deviation). NSP: non-starch polysaccharides. AOAC fibre comprises of the total amount of non-digestible polysaccharides, and includes e.g., lignin and resistant starches, measured with a set of methods developed by the Association of Analytical Chemists (AOAC). Please note the nutritional intake from the intervention sachet is not included in these dietary data. \* Denotes significance.

P values are within group comparisons of the total population between baseline and end of intervention performed using a two-sided paired t-test.

### 3.6 Supplementary Table S6: PROMOTe Dietary Intakes from Background Diet and weight/BMI, by Study Arm

| Dietary variable                          | Baseline       |                |         | End            |                |         | Baseline v
End
Prebiotic | Baseline
v End
Placebo |
|-------------------------------------------|----------------|----------------|---------|----------------|----------------|---------|--------------------------------|------------------------------|
|                                           | Prebiotic arm  | Placebo        | p-value | Prebiotic arm  | Placebo        | p-value | p-value                        | p-value                      |
|                                           | N=36           | N=36           |         | N=36           | N=36           |         |                                |                              |
| Energy, macronutrients, components |                |                |         |                |                |         |                                |                              |
| Energy kcals/d                            | 1581.6 (380.5) | 1557.5 (419.2) | 0.8     | 1449.2 (339.6) | 1500.7 (519.5) | 0.69    | 0.01*                          | 0.30                         |
| Protein g/d                               | 60.5 (17.6)    | 60.0 (12.6)    | 0.91    | 58.0 (14.9)    | 58.3 (21.5)    | 0.95    | 0.44                           | 0.53                         |
| Fat g/d                                   | 70.4 (22.5)    | 61.5 (19.9)    | 0.11    | 61.6 (18.6)    | 63.6 (25.3)    | 0.75    | 0.01*                          | 0.60                         |
| Cholesterol g/d                           | 243.4 (107.7)  | 237.1 (105.9)  | 0.82    | 238.7 (135.6)  | 231.1 (126.8)  | 0.84    | 0.82                           | 0.26                         |
| Carbohydrate g/d                          | 162.0 (52.9)   | 171.6 (66.5)   | 0.54    | 155.0 (43.7)   | 161.4 (69.5)   | 0.71    | 0.06                           | 0.56                         |
| Glucose g/d                               | 13.0 (8.9)     | 13.4 (7.3)     | 0.84    | 12.6 (7.8)     | 13.1 (8.5)     | 0.83    | 0.11                           | 0.87                         |
| Sugar g/d                                 | 71.6 (29.8)    | 76.5 (44.5)    | 0.61    | 67.4 (29.8)    | 71.8 (39.4)    | 0.67    | 0.09                           | 0.51                         |
| Oligosaccharide g/d                       | 1.0 (2.0)      | 0.9 (1.3)      | 0.88    | 0.4 (0.5)      | 0.4 (0.6)      | 0.69    | 0.90                           | 0.23                         |
| Starch g/d                                | 86.3 (34.0)    | 92.7 (36.2)    | 0.48    | 83.2 (30.5)    | 84.9 (37.8)    | 0.87    | 0.15                           | 0.57                         |
| Fibre AOAC g/d                            | 17.0 (6.7)     | 15.6 (4.7)     | 0.34    | 16.1 (4.8)     | 16.6 (8.1)     | 0.8     | 0.33                           | 0.46                         |
| Fibre NSP g/d                             | 12.0 (4.7)     | 10.8 (3.0)     | 0.25    | 11.8 (3.8)     | 11.2 (5.6)     | 0.65    | 0.13                           | 0.68                         |

| Minerals         |                |                |      |                |                |      |       |        |
|------------------|----------------|----------------|------|----------------|----------------|------|-------|--------|
| Sodium mg/d      | 1927.7 (945.2) | 1776.6 (607.2) | 0.47 | 1737.1 (435.4) | 1704.2 (805.0) | 0.86 | 0.20  | 0.996  |
| Potassium mg/d   | 2493.0 (704.8) | 2399.7 (686.7) | 0.61 | 2392.7 (597.9) | 2313.1 (943.2) | 0.73 | 0.05  | 0.50   |
| Calcium mg/d     | 765.4 (319.8)  | 697.9 (217.8)  | 0.35 | 676.1 (239.8)  | 665.7 (470.0)  | 0.92 | 0.07  | 0.88   |
| Magnesium mg/d   | 247.7 (75.6)   | 221.5 (66.3)   | 0.16 | 226.6 (72.6)   | 233.1 (106.3)  | 0.81 | 0.04* | 0.58   |
| Iron mg/d        | 9.0 (2.4)      | 8.7 (2.1)      | 0.64 | 7.8 (2.0)      | 9.2 (5.0)      | 0.22 | 0.06  | 0.54   |
| Zinc mg/d        | 6.9 (2.4)      | 7.0 (2.0)      | 0.89 | 6.7 (2.3)      | 6.7 (2.8)      | 0.97 | 0.38  | 0.26   |
| Selenium µg/d    | 39.7 (17.2)    | 37.7 (15.1)    | 0.63 | 34.5 (16.4)    | 41.2 (18.6)    | 0.19 | 0.73  | 0.80   |
| Vitamins         |                |                |      |                |                |      |       |        |
| Vitamin A µg/d   | 0.0 (0.0)      | 0.0 (0.0)      |      | 0.0 (0.0)      | 0.0 (0.0)      |      |       |        |
| Thiamine mg/d    | 1.2 (0.3)      | 1.2 (0.4)      | 0.51 | 1.2 (0.3)      | 1.5 (1.5)      | 0.37 | 0.48  | 0.73   |
| Riboflavin mg/d  | 1.4 (0.5)      | 1.3 (0.5)      | 0.78 | 1.2 (0.4)      | 1.3 (0.8)      | 0.86 | 0.23  | 0.34   |
| Niacin mg/d      | 14.4 (5.0)     | 14.9 (5.5)     | 0.71 | 14.4 (5.8)     | 16.4 (7.8)     | 0.31 | 0.82  | 0.39   |
| Vitamin B6 µg/d  | 1.4 (0.4)      | 1.6 (0.6)      | 0.25 | 1.4 (0.3)      | 1.4 (0.7)      | 0.99 | 0.41  | 0.31   |
| Vitamin B12 µg/d | 3.7 (1.9)      | 3.6 (2.1)      | 0.78 | 2.8 (1.5)      | 2.8 (1.6)      | 0.96 | 0.54  | <0.01* |
| Folate µg/d      | 221.6 (80.4)   | 218.3 (83.3)   | 0.88 | 200.3 (59.9)   | 182.6 (100.5)  | 0.47 | 0.08  | 0.24   |
| Vitamin C µg/d   | 89.2 (70.3)    | 80.4 (65.1)    | 0.62 | 74.1 (46.0)    | 67.2 (46.6)    | 0.61 | 0.18  | 0.24   |
| Vitamin D µg/d   | 3.6 (4.1)      | 3.0 (2.6)      | 0.51 | 2.6 (2.6)      | 2.4 (2.3)      | 0.7  | 0.92  | 0.05   |

|                              |                |                |      |                |                |       |       |      |
|------------------------------|----------------|----------------|------|----------------|----------------|-------|-------|------|
| 25-Hydroxy Vitamin D3 µg/d   | 0.0 (0.1)      | 0.0 (0.0)      | 0.32 | 0.4 (1.3)      | 0.2 (0.7)      | 0.46  | 0.20  | 0.25 |
| Vitamin D3 µg/d              | 0.3 (0.5)      | 0.5 (0.9)      | 0.19 | 0.2 (0.6)      | 0.4 (0.8)      | 0.34  | 0.96  | 0.15 |
| Vitamin E µg/d               | 9.0 (4.1)      | 7.4 (3.7)      | 0.13 | 6.5 (3.0)      | 6.9 (3.9)      | 0.7   | 0.04* | 0.21 |
| Vitamin K1 µg/d              | 75.1 (92.2)    | 71.0 (69.8)    | 0.85 | 36.8 (36.5)    | 62.0 (43.0)    | 0.035 | 0.35  | 0.79 |
| Food groups and other |                |                |      |                |                |       |       |      |
| Vegetables g/d               | 156.5 (129.5)  | 140.4 (91.5)   | 0.59 | 130.0 (62.2)   | 128.9 (69.9)   | 0.95  | 0.81  | 0.50 |
| Fruit g/d                    | 141.8 (103.4)  | 147.7 (106.4)  | 0.83 | 143.0 (125.3)  | 140.5 (136.7)  | 0.95  | 0.28  | 0.40 |
| Alcohol g/d                  | 11.4 (16.6)    | 11.9 (18.1)    | 0.91 | 9.1 (14.1)     | 9.2 (11.0)     | 0.97  | 0.06  | 0.35 |
| Water g/d                    | 2044.8 (681.6) | 1878.4 (666.1) | 0.35 | 1958.8 (568.1) | 1761.8 (728.0) | 0.3   | 0.57  | 0.12 |
| Weight/BMI            |                |                |      |                |                |       |       |      |
| Weight (kg)                  | 71.8 (14.0)    | 75.8 (17.2)    | 0.28 | 72.7 (13.7)    | 75.0 (15.5)    | 0.54  | 0.58  | 0.68 |
| Body mass index              | 27.3 (5.0)     | 28.7 (5.3)     | 0.24 | 27.7 (4.9)     | 28.3 (4.2)     | 0.57  | 0.51  | 0.58 |

All data presented as mean (standard deviation). NSP: non-starch polysaccharides. AOAC fibre comprises of the total amount of non-digestible polysaccharides, and includes e.g., lignin and resistant starches, measured with a set of methods developed by the Association of Analytical Chemists (AOAC). Please note the nutritional intake from the intervention sachet is not included in these dietary data. \*Denotes statistical significance.

Going from left to right, P values are comparisons between prebiotic and placebo groups at baseline, between prebiotic and placebo groups at study end, within group comparison between baseline and study end for prebiotic arm, and within group comparison between baseline and study end for placebo arm, performed using a two-sided paired t-test.

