#### ***i. Food diary data***

The food diary data will be presented in tables, by sex. Paired tests will be carried out to assess for differences between baseline and study end point, two sample t-tests for continuous variables (normally distributed), and Mann-Whitney test for non-normally distributed continuous variables.

Over and under reporting will be assessed using the Goldberg energy intake to BMR (basal metabolic rate) ratio method . BMR will be calculated using the revised Harris-Benedict equation , and multiplied by an adjustment factor for physical activity . A ratio of this adjusted BMR to energy intake (kcal/day) will be generated. Over and under reporters will be identified as those who are two standard deviations above or below this ratio. If over an/or under reporters are identified, an additional dietary table will be presented, with these participants excluded.

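### The dietary tables print N=72 and N=36 per arm, but only 59 and 48 people have diaries; the number of pairs is not stated, and a minority of baseline-to-end p-values cannot come from a paired t-test on the printed means

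*Combined protocol and SAP*

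**What the plan says.** SAP section 7.1, under Food diary data, plans this: "Paired tests will be carried out to assess for differences between baseline and study end point, two sample t-tests for continuous variables", with Mann-Whitney for non-normal variables. The sentence calls the tests paired but names procedures for two independent samples. The missing-data section of the SAP covers outcomes and baseline covariates. It gives no rule for a diary missing at the end of study.

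Table S4 heads both visits N=56 females, N=16 males and N=72 in total, then shows this row: "Missing Data (n) | 10 | 3 | 13 | | 20 | 4 | 24". Its footnote reads: "P values are within group comparisons of the total population between baseline and end of intervention performed using a two-sided paired t-test". Table S6 heads each arm N=36 at both visits and has no missing-data row. Its footnote describes four p-value columns: between arms at baseline, between arms at the end, a "within group comparison between baseline and study end for prebiotic arm", and the same for the placebo arm. It says all were "performed using a two-sided paired t-test".

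**The concern.** The tables place two visit means side by side with a p-value for the change. A reader takes the p-value to test the difference on view. If the means use everyone with a diary at that visit and the test uses only people with both, the displayed change and the tested change belong to overlapping but unequal sets, and diary drop-out is mixed into the displayed change.

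Participants are told to continue their normal diet, so these tables are where a reader checks whether background diet moved during the trial. That check cannot be read properly when the printed N is too large for the diary rows, the number of pairs is absent, and some p-values visibly disagree with the means beside them.

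**Working it through.** **Coverage (S4 missing-data row).** Baseline: 72 − 13 = 59 (82%), made up of 46 females and 13 males. End: 72 − 24 = 48 (67%), made up of 36 females and 12 males. People with both diaries: at least 59 + 48 − 72 = 35, at most 48. At least 59 − 48 = 11 baseline diarists have no end diary.

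**Which denominator produced the printed totals?** The total mean is the sex-weighted mean of the female and male columns in S4.
- End energy: (36×1410.6 + 12×1672.4)/48 = 1476.05; printed 1476.0. With 56/16 weights: 1468.8.
- End potassium: (36×2252.0 + 12×2649.0)/48 = 2351.25; printed 2351.2. With 56/16: 2340.2.
- Baseline sodium: (46×1723.5 + 13×2312.9)/59 = 1853.37; printed 1853.4. With 56/16: 1854.48.

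The end totals come from 48 people. Most baseline totals fit 59; baseline energy is an exception (1568.98 against a printed 1569.5).

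**Arm sizes (inferred, not stated).** The whole-number splits that best turn the S6 arm means into the S4 totals are 30 prebiotic and 29 placebo at baseline, and 23 and 25 at the end. For instance, (23×1449.2 + 25×1500.7)/48 = 1476.02 for end energy. With 36 people per arm, the number of pairs is then 30 + 23 − 36 = 17 to 23 on prebiotic, and 29 + 25 − 36 = 18 to 25 on placebo.

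**Limits on a paired t-test.** If both columns describe the same n people, the SD of the difference lies between |s1 − s2| (correlation +1) and s1 + s2 (correlation −1). With each mean and SD allowed ±0.05 for rounding, two-sided on n − 1 df:
- largest p: t = (|m1 − m2| − 0.1) / ((s1 + s2 + 0.1)/√n)
- smallest p: t = (|m1 − m2| + 0.1) / ((|s1 − s2| − 0.1)/√n)

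Prebiotic selenium at n = 17: t = 5.1/(33.7/√17) = 0.624, p = 0.54. At n = 8: t = 0.428, p = 0.68. Printed: 0.73.

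Prebiotic fruit runs the other way. At n = 23: t = 1.3/(21.8/√23) = 0.286, p = 0.78. At n = 36: t = 0.358, p = 0.72. Printed: 0.28.

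| S6 row | Baseline | End | Printed p | Attainable, inferred pairs | Attainable, any 8 to 36 pairs |
|---|---|---|---|---|---|
| Selenium, prebiotic | 39.7 (17.2) | 34.5 (16.4) | 0.73 | at most 0.54 | at most 0.68 |
| Oligosaccharide, prebiotic | 1.0 (2.0) | 0.4 (0.5) | 0.90 | at most 0.44 | at most 0.60 |
| Vitamin D, prebiotic | 3.6 (4.1) | 2.6 (2.6) | 0.92 | at most 0.59 | at most 0.72 |
| Vegetables, prebiotic | 156.5 (129.5) | 130.0 (62.2) | 0.81 | at most 0.58 | at most 0.71 |
| Fruit, prebiotic | 141.8 (103.4) | 143.0 (125.3) | 0.28 | 0.78 to 0.98 | at least 0.72 |
| Sodium, placebo | 1776.6 (607.2) | 1704.2 (805.0) | 0.996 | at most 0.83 | at most 0.89 |

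The last column does not depend on the inferred arm split.

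**Extent.** At the inferred numbers of pairs, 12 of 68 within-arm p-values in S6 (34 dietary rows × 2 arms) are unattainable: 7 prebiotic and 5 placebo. Eight of the 12 remain so for any n from 10 to 36. In S4, 2 of the 18 rows checked fail at 35 to 48 pairs: iron is printed 0.892 with at most 0.78 attainable, and selenium 0.998 with at most 0.92. In S5, 6 of 30 rows checked fail.

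**Between-arm columns of S6.** An unpaired t-test at the inferred sizes gives selenium at end 0.19 (printed 0.19), energy at end 0.69 (0.69) and fat at baseline 0.11 (0.11). The single paired label in the footnote does not seem to describe these columns.

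**The case against.** The strongest reply is that available-case means beside a paired test on completers is a common layout, and that S4's missing-data row already tells the reader the columns differ. The p-values may be correct for the people tested. That stands as far as the p-values go: a reader might infer that the tests were miscalculated, and nothing in the documents shows this. It does not rescue the presentation, because the heads state an N that is not the diary denominator, S6 carries no missing count, and the number of pairs appears nowhere.

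A second reply is that a rank test may have been used, since the SAP allows one for skewed variables and oligosaccharide, vitamin D and vegetables look skewed. The limits above would then not apply to those rows, but the footnotes would name the wrong test.

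Third, the consequence is limited. A reader might infer from the fall in prebiotic oligosaccharide (1.0 to 0.4) that diet moved differently by arm. S6 does not support that: placebo goes from 0.9 to 0.4, and the between-arm p at the end is 0.69. The between-arm p-values do not depend on pairing baseline with end. The primary model contains no diary term, and the diet covariate named for the microbiome analyses is the Healthy Eating Index, taken from existing cohort data. All of this stands.

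**Conclusion.** The point holds as a fault in the planned test wording and in the reporting of the dietary tables. Diary coverage is 59 and 48 of 72, with 35 to 48 possible pairs, under heads of 72 and 36 per arm. For a minority of rows the printed p is incompatible with the stated test on the printed means and SDs. Either those means are not the means of the people tested, or a different test was run and the footnote is wrong. The first is the likelier explanation because the totals fit available cases, but the documents do not say so.

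It would be too strong to say that the tables fail throughout, since most rows are compatible with their p-value at some correlation. It would also be too strong to say that the two columns describe different people, since the sets largely overlap. What is affected is the within-arm and whole-group reading of background diet change.

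The incompatibility rests on the footnoted paired t-test having been used and on rounding to one decimal. The count of 12 also rests on the inferred arm sizes; the six rows tabulated do not.

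**What to change.** In SAP 7.1, Food diary data, specify a truly paired comparison among participants with both diaries: a paired t-test, or a paired rank test where the differences are clearly non-normal. Remove the two-sample t-test and Mann-Whitney from that sentence.

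In Tables S4 to S6, give for each baseline-to-end comparison the number of pairs, the mean at each visit in that set, and the mean paired change with its 95% CI. Replace N=72 and N=36 with the actual n for the diary rows. In S6, state this separately from weight and BMI, which are collected by another route and may have a different n. Name the test actually used for each p-value column, including the between-arm ones.

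A mixed model using all diaries is an option, not a requirement.

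The cost is a re-run of existing tables with no new data. The downside is that the displayed paired set is smaller, and people with one diary drop out of the change rows.
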